### Evaluation

4.2

1.Parents satisfaction with the provision of information on the use and safety of CM and their ability to make informed decisions about the use of CM [PS-CATE (38)], [SDM (39)]2.Change in attitudes towards CM, assessed with the Attitudes and Beliefs about Complementary and Alternative Medicine [ABCAM (32)] and the benefits of potentially harmful CM procedures [I-CAM-R (33, 34)]3.Perceived stress of parents, assessed by the Perceived Stress Scale [PSS (40)], and anxiety and depression, assessed by the Patient Health Questionnaire [GAD/PHG (41)], training needs, and content and structural relief of medical staff [LS (35)]4.Attitudes towards CM procedures, assessed by the Complementary and Alternative Medicine Health Belief Questionnaire [CHBQ (42)], knowledge, query, application, reasons for non-application of CM in everyday clinical practice [LS (35)]

### Primary outcome

4.3

These outcome measures are considered in the overall study concept. Using the questionnaires, we examine changes in the above measures of feasibility; and we evaluate the project by interviewing the two cohorts of parents and medical staff before and after the training. The list of these measurement points should not be seen as a ranking, but rather elaborates the hypotheses to be tested: Firstly, whether the project has an influence on parental satisfaction with the information on CM. Secondly, its influence on the ability to make decisions. Thirdly, its influence on attitudes towards CM. Lastly, its influence on perceptions of personal stress levels. For the feasibility of the project, special attention is paid to practicability. The focus is on the different processes that take place at different points in time. Both parents and medical staff as well as the project team should accept the procedures in order for the project to be considered feasible. The completed questionnaires and the qualitative interviews are used to assess acceptance. Furthermore, the number of participants in the questionnaires as well as in the subsequent consultations show whether the project is future-oriented. Minor adjustments should also be feasible afterwards, if relevant for the overall outcome.

### Secondary outcome

4.4

In addition to quantitative data, qualitative data will be assessed using semi-structured interviews of the parent intervention cohort and medical staff. In the *a priori* categorization, gender and age characteristics are taken into account and, in the case of medical staff, also their job description or position in the organization. To ensure the interviewees’ initiative was respected, each interview was limited to 20 min, with a primary focus on identifying barriers to implementation. The pre-developed interview guide shown in Table 1 is intended to identify barriers to the implementation of the CM intervention. Results of the qualitative analysis will be used to improve the CM training and counseling sessions, if necessary, as well as the questionnaire.

**Table 1 T1:** Semi-structured interview guide for parent interviews and interviews with medical staff.

Overview	Content	Parents	Medical staff
Introduction	Welcome and data protection Introduction of the interviewer Procedure and aim of the interview		
Checking the quota criteria	Socio-demographic data of the interviewee	Household/family situation Field of diagnosis	Educational background Job description/field of activities State of knowledge of the SiKOM project
Introductory questions	Definition of CM Attitude towards CM Relevance of CM in (clinical) everyday life	Guiding question: What do you understand by CM? Maintenance question: What else counts as CM for you?	
		What role does CM play in your everyday life? To what extent do you use CM? Can you give an example? To what extent do you ask your doctor about CM? Have there already been conflicts in regard to CM and your child’s current therapy?	What role does CM play in your clinical life? To what extent do parents ask you about CM? To what extent are CM therapies used in your clinic? Can you give an example? Have there already been conflicts in regard to CM and the current therapy of your patients?
Main questions	Bedside CM counseling for families Group training and general information on the project	Guiding question: What should ideal counseling look like for you? Maintenance questions: What do you consider should definitely be part of CM counseling? What should be the central message? Where do you see possible barriers to the introduction of counseling?	Guiding question: What should ideal counseling look like for patients? Maintenance questions: What do you consider should definitely be part of CM counseling for patients? What should be the central message? Where do you see possible barriers to the introduction of counseling? Guiding question: What should training on CM look like for you? Maintenance questions: Which contents must not be missing within the training? Through which channels would you like to be trained? What are strengths of the project, and do you have any concerns about it?
Closing question	Additions Space for questions from the interviewee		
Conclusion	Acknowledgement Farewell		

### Data analysis

4.5

Frequent communication between the project team and contact persons at the respective pediatric oncology departments and the parents, as well as the regular on-site monitoring of the study team, will ensure the correctness and quality of the data generated. All parent and staff questionnaires from the five centers are stored separately from the consent forms. The questionnaires to be evaluated are only available to the statistician in a pseudonymized form. Pseudonymization involves the removal of personal identifiers and their substitution with placeholder values, typically composed of a sequence of numbers and letters, so it is not possible to draw conclusions about the individual participants. The data analysis is carried out by IBM® SPSS. The questionnaires are entered manually into SPSS and checked for transmission errors using the dual control principle with the original data.

Qualitative data will be audio-recorded, transcribed verbatim, anonymized, and then coded and analyzed according to qualitative content analysis (43, 44) using MAXQDA software. The analysis follows an inductive approach, as the categories were independently developed based on our research question.

To evaluate the feasibility and determine whether the intervention is suitable for progression to a larger effectiveness trial, specific progression criteria have been established. Recruitment feasibility will be assessed by the ability to recruit the planned sample size of 100 medical staff and 50 parents within the study period, with an acceptable participation rate and minimal refusal. Retention rates are also critical, with at least 80% of participants expected to remain engaged throughout the study, and reasons for dropouts systematically documented. The acceptability of the intervention will be evaluated using the Acceptability of Intervention Measure (AIM) and qualitative feedback, with positive feedback from at least 70% of participants serving as a benchmark.

Additionally, compliance will be assessed by ensuring that at least 80% of planned counseling sessions are completed, while any barriers to implementation, such as logistical or organizational challenges, will be identified through qualitative interviews with staff. Data quality is another essential criterion, with at least 90% of collected questionnaires expected to be complete and analyzable to ensure the reliability of feasibility and outcome measures. Finally, satisfaction rates among parents and medical staff regarding counseling content and delivery will be monitored, and specific barriers to implementation will be identified through semi-structured interviews.

These criteria provide a structured basis for determining the feasibility of the intervention and whether it warrants further investigation in a fully powered randomized controlled trial (RCT). If certain criteria are not met, modifications may be made, and feasibility reassessed in subsequent phases.

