-Vestische Children's and Youth Hospital Datteln, Germany-Pediatric Hematology/Oncology, Dortmund Hospital, Germany-Department of Pediatrics and Adolescent Medicine, University Hospital Essen, Germany-Pediatric Hematology/Oncology, University Hospital Cologne, GermanyThe Rhine-Ruhr metropolitan area is beneficial for the fact that there are many oncological centers in a very small area, so that the treatment team can drive to them and deliver bedside counseling and support in presence. By selecting a prospective, multicenter study design, two cohorts of parents of children with a diagnosis of cancer and one cohort of medical staff from the participating pediatric oncology departments can be included. Sociodemographic data will be collected from all cohorts, with particular emphasis on the educational level of the parents, to determine whether education influences responses in the surveys. While one parent cohort will receive CM counseling, the other will serve as a waitlist cohort to be offered the respective CM counseling after the outcome assessment. Group assignment will be non-randomized by starting with a control cohort followed by the intervention cohort. After being informed about the study during the initial visit by their treating physician and signing written informed consent, parent cohorts will receive standard questionnaires three weeks after study inclusion. For the parent control cohort, the CM counseling will take place after this outcome assessment, while the parent intervention cohort will receive CM counseling before. Outcomes will be compared between groups. Medical staff will be trained in CM counseling strategies and assessed before and after the CM training. Outcomes will be compared within this group. A summary of the study design can be found in Figure 1. The active study period of recruiting is scheduled from December 2022 to end of 2027. Since there are five participating centers and a small project team, the time invested to be able to include subjects in the study will be in relation to the effort involved. For the medical staff, 100 participants are considered an acceptable and desirable number. Traveling to the study centers and maintaining contact with parents requires resources. The sample size for the survey and consultation includes 50 participants, evenly divided into two cohorts of 25 individuals each. We also expect a dropout of 10%, as parents who find themselves in such a difficult situation might also turn away.

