## Outcomes

4

All participants will be asked about baseline social demographics. Data on pediatric cancer characteristic will be obtained from medical records. Both cohorts of parents receive one questionnaire each, while medical staff receive questionnaires twice, once before and once after the CM training (see Figure 2). The questionnaires refer to the objectives already mentioned above in the protocol.

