### Statistics

4.6

As this is an exploratory study, the sample size was not predetermined. However, a target of 100 participants for the cohort of medical staff, along with two groups of 25 participants each for the parent cohort has been set. The chosen sample sizes are justified based on feasibility considerations and the estimated response rates. Across the four study centers, an average of five new patients are admitted each month. All eligible patients and their parents who do not immediately decline participation will be included in the study. Based on prior experiences, it is estimated that approximately 50% of distributed questionnaires will be returned completed.

This corresponds to an expected return of around 2–3 questionnaires per month per center from the parents. With these projections, the parent cohort would reach the target size of 50 participants within approximately 6–8 months. For the cohort of medical staff, which is relatively stable in size, we anticipate achieving the target sample size within a similar period, assuming a participation rate of around 70%. A 95% confidence interval will be calculated for the proportion of participants who return completed questionnaires, allowing us to assess the precision of our estimates. This approach ensures that the sample size is sufficient to explore key outcomes while remaining realistic and aligned with the study's feasibility constraints.

The statistical analysis plan includes descriptive statistics for sample characteristics, feasibility, and effectiveness outcomes. Descriptive statistics comprise percentages for categorical variables and means with standard deviations for continuous variables. Feasibility results are analyzed by reporting the number and proportion of parents screened, enrolled, and counseled during the study period, along with retention and dropout rates. Reasons for dropouts are categorized and analyzed descriptively. Subgroup analyses explore variability across demographic groups, and qualitative interviews provide additional insights into perceived acceptability. For medical staff, feasibility is measured using the Feasibility of Intervention Measure (FIM), with descriptive statistics summarizing scores and qualitative interviews identifying barriers to implementation. Completion rates of planned counseling sessions are also reported descriptively, and differences across study centers are explored using chi-squared tests or Fisher's exact tests.

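### The 80% retention criterion has no stated denominator or event, and the plan's own 50% return and 10% dropout figures give opposite verdicts on it for parents

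*Protocol article*

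**What the plan says.** All of the following is in the protocol article.

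- **Entry (3.1 and 4.6).** Parents are told about the study, sign consent and are included. Section 4.6 adds: "All eligible patients and their parents who do not immediately decline participation will be included in the study".
- **Parent assessment (3.1 and 4).** After that, "parent cohorts will receive standard questionnaires three weeks after study inclusion". Section 4 confirms the number: "Both cohorts of parents receive one questionnaire each".
- **Expected return (4.6).** From prior experience, "it is estimated that approximately 50% of distributed questionnaires will be returned completed". This is turned into 2–3 returns per month per center, and from there into 50 parents in about 6–8 months.
- **Expected dropout (3.1).** "We also expect a dropout of 10%, as parents who find themselves in such a difficult situation might also turn away".
- **Target (3.1).** "The sample size for the survey and consultation includes 50 participants, evenly divided into two cohorts of 25 individuals each". Section 4.5 restates the target as 50 parents and 100 medical staff to be recruited.
- **Progression criterion (4.5).** Retention is called critical, "with at least 80% of participants expected to remain engaged throughout the study".

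No event that counts as remaining engaged is given, and no denominator. Nor is it said whether the 80% applies to parents, to staff or to both together.

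**The concern.** On the sequence described, the questionnaire goes to parents who have already consented and been included. A parent who does not send it back is an included participant without outcome data. Section 4.6 expects that of about half the parents, while section 3.1 expects to lose one in ten. Both cannot be the total loss in the same group, and nothing in the article says that they refer to different groups.

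The word participants does not settle the matter, because section 4.6 uses it in two ways. The target of 50 participants is built up from returned questionnaires, so there a participant is someone who has responded. The same section plans a 95% confidence interval for the share of participants who return a completed questionnaire, so there non-responders are participants too.

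Feasibility is the main objective, and the criteria in section 4.5 are meant to inform whether a fully powered randomized trial is warranted. If the denominator is left open, it can be chosen once the returns are known, and that choice can decide whether the criterion is met.

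**Working it through.** **Inputs.** Return 50% (4.6); dropout 10%, so 90% kept (3.1); threshold 80% (4.5); parents 50, as 2 × 25 (3.1); staff 100 (4.6); five admissions and 2–3 returns per month, the latter per center, and four centers (4.6).

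**Step 1: what the plan's own projection counts.** Five admissions × 50% = 2.5, which matches 2–3 returns per month per center if the five admissions are per center. Months to 50 at four centers = 50 / (4 × returns per center):

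- 2 returns: 50/8 = 6.25
- 2.5 returns: 50/10 = 5.0
- 3 returns: 50/12 = 4.2

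Only the lowest rate falls in the stated 6–8 months. That mismatch is a separate matter. The use here is to see what the 50 counts. Without the 50%, four centers × 5 = 20 parents per month would reach 50 in 2.5 months, well short of 6–8. So in section 4.6 the 50 are returned questionnaires, with the 50% already taken off. At that rate 50/0.5 = 100 parents must be given a questionnaire.

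**Step 2: chance of meeting 80% if retention means returning the questionnaire.** With X ~ Binomial(n, p), the criterion is met if X ≥ 0.8n.

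| Included parents | Needed | p = 0.50 | p = 0.90 |
|---|---|---|---|
| 25 | 20 | 0.0020 | 0.967 |
| 50 | 40 | 0.000012 | 0.991 |
| 100 | 80 | 5.6 × 10⁻¹⁰ | 0.999 |

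**Step 3: can the two figures be nested?** If 10% withdraw and overall return is 50%, return among those who stay is 0.50/0.90 = 56%. This is possible arithmetically, but total loss is then 50%, and the plan would have to say that non-return is not dropout.

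**Step 4: if the criterion pools parents and staff.** With 50 parents and 100 staff, 120 of 150 must be retained. The article gives no staff retention (its 70% is a participation rate), so the range below is an assumption. The probability is that of the sum of two independent binomials.

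| Assumed staff retention | Parents at 50% | Parents at 90% |
|---|---|---|
| 80% | 0.003 | 0.886 |
| 90% | 0.17 | >0.999 |
| 95% | 0.55 | >0.999 |
| 100% | 0.94 | >0.999 |

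Pooling does not remove the dependence on which parent figure applies, except when staff retention is close to complete.

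**The case against.** The strongest reply is that staying engaged need not mean returning one form. Control parents are offered counseling after the questionnaire (3.1), the intervention allows an ongoing exchange (3.4), and interviews are planned in the intervention cohort (4.4). Section 4.6 also treats the questionnaire return proportion and the retention and dropout rates in different paragraphs. The 50% could then be a response yield that never enters retention. This stands to the extent that the article does not equate the two. It does not close the gap: no other retention event is given, and if only responders count as participants, questionnaire retention is complete by construction and the criterion tests nothing on that measure.

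Three stronger readings are tempting, and the article does not support them.

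- **A three-way conflict between 10%, 80% and 50%.** The 10% is an expectation and the 80% a minimum. An expected 90% kept lies above the minimum, so these two agree. The tension is with the 50% alone.
- **The criterion is almost certain to fail.** That requires retention to mean questionnaire return among included parents only. The article does not say so, and participants may include the staff, for whom the 50% is not used.
- **Only 25 analysable parents in all.** Section 4.6 derives its 50 from returns, so halving it again would count the same loss twice.

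It can also be said that definitions belong in the full protocol or analysis plan. As to missing detail that is fair. Here, however, the article itself prints figures that do not fit together.

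**Conclusion.** The concern holds in a limited form. A 50% return and a 10% dropout cannot both be the total loss among included parents, and the 80% criterion does not say which applies. Under the reading that retention is return of the three-week questionnaire by included parents, the chance of meeting it is 0.2% (n = 25) or 0.001% (n = 50) with one of the plan's figures, and 97% or 99% with the other. These values assume independent parents and take each figure as the true rate. They show how far the verdict depends on an open definition; they do not predict failure. Separately, the 50 parents are recruits in section 4.5 and returned questionnaires in section 4.6.

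The stakes are moderate. Retention is one of several criteria, and section 4.5 answers a missed criterion with modification and reassessment, not with a stop. The point should be fixed, but it does not invalidate the design.

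**What to change.** Reconcile sections 3.1, 4.5 and 4.6.

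1. Define parent retention as completed three-week questionnaires divided by consented parents, reported per cohort with an exact 95% confidence interval.
2. Define staff retention separately, as both questionnaires returned, and apply the 80% to each group rather than to an unnamed total.
3. State whether the 50 means consented parents or returned questionnaires, and use that meaning in all three sections.
4. Choose one of two consistent versions:
   - The 50% is return among included parents. State that about 50/0.5 = 100 parents must be included to obtain 50 returns, and restate the 10% dropout and the retention benchmark to fit.
   - The 50% is response before consent. Say so, keep 10% and 80%, and state that 50 consented parents yield about 50 × 0.9 = 45 analysable, or 50 × 0.8 = 40 at the benchmark.

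The cost is rewording in three sections. In the first version, the number of parents to be included rises to about 100 and the dropout and retention figures become less favorable. In the second, the expected number of analysable parents falls from 50 to about 45. No new data collection is needed to apply the definitions.

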### Interventional methods

3.4

The intervention for parents will include a half-hour CM counseling session at the respective treatment center and, if necessary, an ongoing exchange. The personal counseling and support are planned to take place directly at the bedside and includes advice on how to safely use CM therapies in addition to conventional cancer therapy. In this setting, parents have the opportunity to ask questions of interest about CM. To ensure comprehensive reporting and implementation of the intervention, we will utilize the Template for Intervention Description and Replication (TiDier) framework (30). This framework will guide the detailed description of the intervention components, delivery methods, and the context in which it is implemented. Additionally, a fidelity checklist, informed by the GRIPP2 reporting framework, will be employed to assess the consistency and accuracy in delivering the intervention across different sites and facilitators (31).

The intervention for the medical staff will consist of frontal training units on the communication of CM topics mainly related to the effects, adverse events and interactions of different CM therapies with conventional cancer treatment. This is supplemented by case-based training in each of the five participating centers.

For the parent intervention cohort as well as the medical staff cohort, evidence-based information is made available on the SiKOM homepage (www.sikom.info) and by means of brochures for all those interested in further CM information. Moreover, study participants have the opportunity to ask questions or receive information on individual concerns via a telephone hotline, which is available throughout the entire duration of the project.

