### Feasibility

4.1

1.Attitudes towards [ABCAM (32)], previous experience with [I-CAM-R (33, 34)] and support needs (LS (35) regarding CM of parents of children with cancer2.Number of parents who can be screened, enrolled and counseled during the study period, number of medical staff, study-related retention and dropout rates, reasons for study dropouts3.Acceptability of the CM intervention (parent intervention cohort only), assessed with the Acceptability of Intervention Measure [AIM (36)]4.Proportion of planned consultations that could be completed, feasibility of the intervention by medical staff [FIM (36)]5.Acceptability of the overall approach within the project is assessed in a targeted sample of parents and medical staff [TFA (37)].

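### The 80% delivery criterion is not restricted to the intervention cohort or to sessions held before the questionnaire, so it can be met while timely counseling falls well short

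*Protocol article*

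**What the plan says.** The Data analysis section (4.5) of the protocol article lists criteria for deciding whether to move on to a larger trial. The one on delivery is that "compliance will be assessed by ensuring that at least 80% of planned counseling sessions are completed". The matching outcome, item 4 in the Feasibility section (4.1), is "Proportion of planned consultations that could be completed". The Statistics section (4.6) adds: "Completion rates of planned counseling sessions are also reported descriptively, and differences across study centers are explored". None of the three names a cohort or a time window.

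Study setting and design (3.1) gives the structure behind these counts:

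- On size: "The sample size for the survey and consultation includes 50 participants, evenly divided into two cohorts of 25 individuals each".
- On outcome timing: "parent cohorts will receive standard questionnaires three weeks after study inclusion". The Outcomes section (4) gives each parent cohort one questionnaire only.
- On the order of events, for the control cohort "the CM counseling will take place after this outcome assessment, while the parent intervention cohort will receive CM counseling before".
- The control cohort is described as follows: "the other will serve as a waitlist cohort to be offered the respective CM counseling after the outcome assessment".

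Interventional methods (3.4) describes the parent intervention as "a half-hour CM counseling session at the respective treatment center and, if necessary, an ongoing exchange".

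**The concern.** With one questionnaire per parent and no randomization, the cohorts differ by design in one respect: whether the family was counseled before the three-week questionnaire. The second feasibility question in the Objectives asks whether the intervention can be implemented as the protocol lays down. For the intervention cohort, that means a session inside the three weeks.

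The criterion measures something looser. It counts planned sessions, and waitlist sessions are planned too. It carries no date condition. Its denominator is planned sessions rather than enrolled parents, so it does not say how to treat a parent for whom no session was ever arranged.

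The two cohorts are also not equally easy to serve. No deadline is stated for waitlist sessions. Intervention sessions must fit into three weeks from inclusion, with a small team travelling between centers and parents whom the Limitations section describes as heavily burdened. Late or missed sessions in the intervention cohort are the failure a feasibility study most needs to detect, and waitlist sessions could mask it.

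At stake is the decision on whether a fully powered randomized trial is warranted. In addition, if uncounseled parents stay in their assigned cohort for analysis, the between-cohort comparisons in Statistics are weakened.

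**Working it through.** **Inputs.** Threshold 80% (Data analysis). Two parent cohorts of 25 (Study setting and design). Expected dropout 10% (same section). One planned session per family is an assumption, based on the single half-hour session in Interventional methods.

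**The plan's own figures.** 25 + 25 = 50 reproduces the stated parent total. The 80% is a chosen benchmark with no formula behind it.

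**Does the text pool the cohorts?** Counseling is planned for both, and the total of 50 is given for survey and consultation together. In the Feasibility list, item 3 (acceptability) is expressly limited to the parent intervention cohort; item 4 (completed consultations) has no such limit. The plain reading is therefore a pooled count.

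**Pooled bound.** Let nI and nC be the planned intervention and waitlist sessions, and w the waitlist sessions completed.

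- Sessions needed = ceil(0.8 × (nI + nC)) = ceil(0.8 × 50) = 40.
- Minimum intervention sessions = 40 − w.
- Largest intervention shortfall = (25 − (40 − w)) / 25.

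| Waitlist sessions completed (w) | Intervention sessions needed | Intervention families uncounseled |
|---|---|---|
| 25 of 25 | 15 | 10/25 = 40% |
| 23 of 25 | 17 | 8/25 = 32% |
| 20 of 25 | 20 | 5/25 = 20% |
| 15 of 25 | 25 | 0/25 = 0% |

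**With about 10% dropout** (22 or 23 families per cohort, all waitlist sessions completed):

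- 22 and 22: need ceil(0.8 × 44) = 36, so 36 − 22 = 14 intervention sessions; 8/22 = 36% uncounseled.
- 22 intervention and 23 waitlist: need ceil(0.8 × 45) = 36, so 36 − 23 = 13; 9/22 = 41% uncounseled.

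The bound is thus 36% to 41%.

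**Timing.** The 40% comes from pooling alone. If a session held after the questionnaire also counts as completed, all 25 intervention sessions could take place late. The criterion would then be met with 25/25 uncounseled at assessment, so it sets no limit on timely delivery.

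**Under a restricted criterion.** Counting only intervention-cohort parents counseled before the questionnaire: ceil(0.8 × 25) = 20 needed, so at most 5/25 = 20% missed.

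**The case against.** The strongest reply is that the article is silent rather than wrong. It limits the count to planned counseling, and for the intervention cohort the plan is counseling before the questionnaire, so a late session could fairly be read as not completed as planned. An article may also leave counting rules to a fuller document. The first part stands this far: a reader might infer that sessions of any kind, cohort or date are credited, and the text does not say so. The second part does not dispose of the point. The article itself presents these criteria as established and fixes this one as a percentage of a named denominator, and that stated measure does not match what the design requires.

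A second reply is that other items would reveal a shortfall. Statistics reports the number and proportion of parents screened, enrolled and counseled; there is a fidelity checklist; barriers are explored in interviews; and the 80% is one criterion among several. These help, but the count of counseled parents refers to the whole study period and has no threshold. The completion rate is compared across centers, not cohorts, and no timing element is stated for the checklist. An uncounseled parent who returns a complete questionnaire would count in favor of the data-quality criterion.

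A third reply is that 40% is a worst case. That stands. It needs complete uptake of what is only an offer to waitlist families. With equal completion in both cohorts the shortfall is 20%, the same as a restricted criterion would allow.

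A reader might also infer that follow-up contacts can inflate the rate. The documents do not support resting the point on this: the ongoing exchange is as needed and is not clearly a planned session.

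**Conclusion.** The concern holds as a defect in how a go/no-go measure is defined. The 80% threshold itself is not wrong and contradicts nothing in the article; what is missing is the restriction to the intervention cohort and to the time before the questionnaire.

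The size is conditional. With pooling, one planned session per family and no dropout, up to 10 of 25 (40%) intervention families could be uncounseled while the criterion is met. The figure drops as waitlist uptake drops. Under the further assumption that late sessions count, there is no limit at all. These are bounds on what the criterion would let through, not forecasts of delivery.

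A reader might go on to conclude that the comparisons are certain to be diluted. The article does not define the analysis population, so that follows only if uncounseled parents are analyzed with their cohort.

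The change is worth making before the criterion is applied, because it bears directly on the decision the study exists to inform.

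**What to change.** Replace the delivery criterion with a per-parent one: at least 80% of enrolled intervention-cohort parents received the half-hour counseling session before their three-week questionnaire. Use enrolled parents as the denominator, so that a parent never scheduled counts as not reached. Align item 4 of the Feasibility section with this wording. Report waitlist sessions and follow-up contacts separately, outside the criterion.

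The existing 80% and the three-week questionnaire stay as they are. The cost is one rewritten sentence and use of each session's date. The completion rate may look less favorable. The change brings missed timely delivery into the progression decision; it does not remove dilution from the between-cohort comparisons, since uncounseled parents may still be in them.
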